## Abstract

**Background:**

Children with poor motor ability have been found to engage less in physical activities than other children, and a lack of physical activity has been linked to problems such as obesity, lowered bone mineral density and cardiovascular risk factors. Furthermore, if children are confident with their fine and gross motor skills, they are more likely to engage in physical activities such as sports, crafts, dancing and other physical activity programs outside of the school curriculum which are important activities for psychosocial development. The primary objective of this project is to comprehensively evaluate a whole of class physical activity program called *Animal Fun *designed for Pre-Primary children. This program was designed to improve the child's movement skills, both fine and gross, and their perceptions of their movement ability, promote appropriate social skills and improve social-emotional development.

**Methods:**

The proposed randomized and controlled trial uses a multivariate nested cohort design to examine the physical (motor coordination) and psychosocial (self perceptions, anxiety, social competence) outcomes of the program. The *Animal Fun *program is a teacher delivered universal program incorporating animal actions to facilitate motor skill and social skill acquisition and practice. Pre-intervention scores on motor and psychosocial variables for six control schools and six intervention schools will be compared with post-intervention scores (end of Pre-Primary year) and scores taken 12 months later after the children's transition to primary school Year 1. 520 children aged 4.5 to 6 years will be recruited and it is anticipated that 360 children will be retained to the 1 year follow-up. There will be equal numbers of boys and girls.

**Discussion:**

If this program is found to improve the child's motor and psychosocial skills, this will assist in the child's transition into the first year of school. As a result of these changes, it is anticipated that children will have greater enjoyment participating in physical activities which will further promote long term physical and mental health.

**Trial registration:**

This trial is registered in the Australian and New Zealand Clinical trials Registry (ACTRN12609000869279).

## Background

Movement in children is critical to physical, mental, and emotional adjustment in childhood and adolescence [1]. Key child health issues of international importance include childhood obesity, and its serious health implications, and mental health issues such as anxiety and depression.

The world prevalence of overweight in school-aged children has been estimated at 10% with 25% of these being obese [2]. Furthermore, this proportion continues to rise, particularly in economically developed regions such as Canada and Australia. However, interventions targeting diet and/or physical activity have had limited success [3]. Furthermore, childhood overweight/obesity is not just associated with poor physical health but also poor psychosocial health, particularly in boys [4].

Anxiety and depression are the most common mental health problems experienced by Australian children and adolescents [5], and are significant problems worldwide [6]. Depressive disorders have been estimated to have a lifetime prevalence in adolescence of between 15 - 20% and 6 month prevalence in adolescence of between 5 - 6% and between 1 - 3% in children [7,8]. The 12 month prevalence rates for anxiety disorders are approximately 8% in children and between 11% and 20% in adolescents [9]. Internalising problems such as anxiety and depression are particularly burdensome for children, interfering with social, cognitive, emotional, and academic life at a time when other children are building skills and competencies [10,11].

### Motor ability is linked with obesity and mental health

In addressing these two key childhood issues of obesity and poor mental health, an approach that has been overlooked is one which links these problems in early development, namely their relationship with motor ability.

It is well established that a lack of physical activity is considered a key factor underlying childhood obesity [12], and a lack of physical activity has been linked to other problems such as lower mineral density and cardiovascular risk factors [13]. Children with poor motor ability have been found to engage less in physical activities than other children [14]. To engage successfully in physical activities children need to have a certain degree of motor competence, and competence motivation theorists such as Harter [15] argue that confidence in his or her own ability to perform any activity partly determines the child's involvement level. If children are confident with their motor skills, they are more likely to engage in physical activities such as sports, dancing and other physical activity programs outside of the school curriculum [16]. Trost et al. [12] found that in sixth grade children, physical activity self-efficacy was a key variable which distinguished the obese and non-obese children. Previous research [1,17]has demonstrated that children with poor motor ability perceive themselves as less athletically competent, which has been linked to higher levels of anxiety [1] and depressive symptomatology [18].

Schoemaker and Kalverboer [19] established a link between motor coordination difficulties and social and affective problems in children as young as 6 years. Since then, research has identified that children with motor deficits have social and emotional problems such as poorer self-worth [1,20], and have higher levels of anxiety [1,21], and depression [18,22]. Piek, Bradbury et al.'s study [21] found that kindergarten children's level of motor coordination was negatively related to anxious/depressed behavior as reported by the mother, which is consistent with the finding for older children. However, this finding is of serious concern as these children were only 4-5 years of age. Furthermore, recent findings have shown that gross motor performance in infancy and early childhood predict later anxiety and depressive symptomatology in school age children [23], and if young school-age children have both motor and anxiety problems they are more likely to have psychosocial difficulties in adolescence [24].

### Motor ability is linked with other aspects of development

Until recently, there has been little evidence provided for a relationship between motor ability and other aspects of development such as cognitive and language development. However, recently, an association between early development of gross motor skills and later cognitive abilities in children [25] and adults [26] has been identified. Other research [27] has found that motor ability in children is related to cognitive, language and empathic ability. Children with poor motor ability have been found to perform more poorly on cognitive tasks such as working memory [25,28], and emotional recognition [29]. Poor motor ability is also associated with many of the major developmental disorders such as Attention Deficit Hyperactivity Disorder [30,31], language impairment [32], Reading Disability [33] and Autism [34]. Many of these disorders have been found to be comorbid with Developmental Coordination Disorder (DCD), recognised by the American Psychiatric Association through its inclusion in the DSM-III in 1987 and in subsequent editions [35]. Children with DCD have a significant impairment in their motor coordination that cannot be attributed to any neurological deficit.

A recent study by Bart, Hajami and Var-Haim [36] identified the importance of motor ability in kindergarten on the transition to school. They found that motor function at the kindergarten (equivalent to our Pre-Primary) stage was predictive of scholastic adaptation and social and emotional adjustment 12 months later in the child's first year of school. This finding is particularly relevant to the proposed project.

### Interventions to improve motor ability

Despite the importance of motor development, there has been surprisingly little research examining the most effective way of teaching motor skills in schools. A primary focus has been on physical activity and sport skills, but there has been less emphasis on appropriate skill development for everyday functioning, particularly fine motor ability that is crucial for skills such as hand-writing. There are many motor skills programs currently available, but there is little information on how effective they are, and few have been developed for the Pre-Primary age. The *Move it Groove it *program, based in the state of New South Wales in Australia, was developed for 8 to 10 year olds [37]. Based on the mastery of fundamental movement skills (FMS), the developers of this program argued that it produced substantial improvement in movement skills over a relatively short period of time. Another program that relies on the development of FMS is the *FMS program *[38] that has been adopted by the Department of Education in Western Australia. There are three categories of skills that are included, body management (4 skills); locomotor skills (9 skills) and object control (9 skills - all ball skills). The argument behind this approach is that fundamental skills such as running, throwing, skipping and balancing are the building blocks for improving more complex sports. As mentioned before, the focus is on sports and physical activity participation. The latter program has not had any published reviews of its efficacy. The *Sports Play and Recreation for Kids *program [39] was developed in the US for elementary students and has been evaluated. This program included classes taught by movement experts as well as others by trained teachers. Both were found to increase physical activity levels *in class*. They also demonstrated improved movement skills. However, in all of these programs there is a lack of emphasis on fine motor ability, and it is known that both fine and gross motor ability are important for appropriate skill and mental health development [40]. In particular, poor motor ability has been linked to poor visual-spatial organisation [41,42], and this component needs to be more seriously considered in early movement programs.

According to Trost et al. [43], the following are important to include in physical activity intervention programs for children:

(1) provide activities that are developmentally appropriate so children can succeed

(2) provide the opportunity to observe influential others such as parents and peers performing physical activity

(3) provide verbal encouragement to participate

(4) reduce or eliminate grading or competition in the activity in order to reduce anxiety.

Another important factor is to ensure that the program is inclusive, that is, adopting a universal program for all children within the class. By including all children it reduces the stigma associated with being placed into a 'special' program. Furthermore, given that socially disadvantaged children are generally at higher risk for physical and mental health problems [44], universal interventions with socially disadvantaged children are likely to help prevent a higher proportion of problems in these children. For sustainability and continuity to be maximised it has also been argued that community interventions based in the school or home environment are the most appropriate places for universal interventions to occur [45]. Including all children is a challenge, as it means it must be interesting and exciting for those students who are both physically and socially competent, while being easy enough for the students who are struggling.

In order to accommodate both these needs, the program needs to provide considerable flexibility. These were the key concerns when developing the *Animal Fun *program.

### The Animal Fun program

The *Animal Fun *program is a Pre-Primary program developed to promote motor and social development. It includes four modules focusing on gross motor development, four modules focusing on fine motor development, and a module on social/emotional development.

The gross motor modules are designed to promote good static and dynamic balance, increase strength in lower limb muscles, and to develop an interest in locomotor activities such as running, skipping, jumping, climbing and hopping, correct techniques for throwing, catching and kicking, and more complex movement based on combining movements together.

The fine motor modules include activities that develop postural stability, and strengthen shoulder, elbow, wrist and hand muscles. They are also designed to develop sequencing in fine motor activities, and promote pre-scissor and pre-writing skills. The more advanced skills involve tool manipulation and the development of successful, mature and functional use of pencils, scissors, keyboards, mouse and joystick.

The social/emotional module includes activities where children are taught to accurately identify, label and monitor their feelings [46]. It is based on the Aussie Optimism program (AOP) developed by [name] [47] and adapted for younger children by [name] [48].The Aussie Optimism Feelings and Friends Program is a 10-module program that has been adapted for year 1 and 2 students as well as a version for slightly older students in year 3 whose reading and writing skills and emotional repertoire is more developed. The programs include cognitive and behavioural intervention strategies and targets social, emotional and cognitive risk and protective factors for anxiety and depression. In modifying this for Pre-Primary children, the *Animal Fun *program has focused on the modules of Laughter, Identifying and labeling feelings, Breathing, and Relaxation.

The movement components of the *Animal Fun *program were developed based on the principle that to be successful in movement activities, children need to have a degree of motor competence, plus confidence in their ability to perform the activity [49]. Appropriate technique is an important aspect of motor skill development. However, research demonstrates that if children enjoy movement activities then it is more likely that they will participate, and will begin to build skills [50]. Participation promotes social interaction but also leads to practice which is the key to improving skills. In other words, if the children enjoy what they are doing, they will practice it and will improve their skills. Another key principle is how meaningful it is to the child [50]. By imitating animals as part of the program, the child can attach meaning to the tasks which adds to the fun and enjoyment.

The *Animal Fun *program was developed in consultation with teachers, developmental and clinical psychologists, physiotherapists, occupational therapists, speech therapists and health professionals working in the field with children who have motor disorders. The process involved an 8 month initial development followed by a pilot study and subsequent program refinement.

The pilot study was conducted with 120 children from 3 schools in low socioeconomic areas, with one school having the intervention and the other two smaller schools as controls. Pre-testing occurred in school term 1, the *Animal Fun *program was delivered in school terms 2 and 3, and post-testing occurred in term 4. Both motor and psychosocial variables were recorded pre- and post- intervention. Given the short time-frame, improvement in motor development was not anticipated (and not found) at post-testing, although it was anticipated that it would be observed later in development, hence the need to follow the children's progress into Year 1.

However, there were very promising psychosocial findings. Teachers returned 87 *Social Skills Rating Scales (teacher version) *forms, and a MANCOVA including all three subtests (cooperation, self-control and assertion) gave a statistically significant time x group interaction (F(3, 81) = 10.363, p < .001; partial η^2 ^= .277). Univariate analyses showed that the intervention produced a significant improvement in cooperation (F(1,83) = 21.507, p < .001; partial η^2 ^= .206). Behavioural measures of internalising, externalising, problem behaviour and academic competence failed to reach significance but all showed improvements in the predicted direction for the intervention group. At the conclusion of the post-testing, a focus group was run to determine the teachers' views on the program. All teachers found it easy to incorporate into the curriculum, and all were positive about the program with some of the comments as follows: The program was "really fun -the kids love it"; "easy to use and easy to follow"; "flexible", "was very adaptable"; "very little preparation time"; "good range of difficulty levels"; "all children joined in" With pilot study results showing an improvement in social skills and greater power being needed to evaluate the other potentially beneficial effects of the program, a large randomised controlled trial evaluating the efficacy of *Animal Fun *is needed.

In addition to the importance of motor ability for physical activity and fine motor skills such as hand-writing, movement skills are also linked with social interaction and social-emotional adjustment. There is also evidence that the early years before formal school may be an important time to invest in motor development given its relationship with the transition to school [36]. Given the promising results provided by our pilot study for the *Animal Fun *program, the current study proposes to evaluate the program in a randomised control trial with a larger sample of Pre-Primary children in both metropolitan and regional schools, to determine the impact on motor and psychosocial development immediately after the intervention and then 12 months following intervention once the child has entered grade 1 of school.

## Methods/Design

### Design and Aims

This study will use a randomized, cluster controlled trial to examine the influence of a school-based movement and psychosocial program on the physical and mental health of young children in their first years of school. A multivariate nested cohort design [51] will be used to examine the physical (motor coordination; BMI) and psychosocial (self perceptions, anxiety, social competence) outcomes of the program at the end of the Pre-Primary year and also 1 year later after the transition to primary school. Pre-intervention scores on motor and psychosocial variables for both control and intervention schools will be compared with post-intervention scores and scores taken 12 months later in Year 1.

### Participants

Twelve government primary schools from both metropolitan and regional areas will be invited to participate in this project. It is anticipated that 8 schools will commence in the first year of the study with the remaining 4 the following year with half being allocated as intervention schools and the other as control schools. Schools will have 50 or more students (two or more classes) enrolled in Pre-Primary classes for children aged 4 or 5 years. Schools from low socio-economic areas with a decile ranking of 7 or above will be targeted as it is anticipated they will have higher rates of physical and mental problems [44]. Regional centres will be included as they have been identified as areas in need of assistance, particularly as there are limited resources available for children with movement and psychosocial problems, and high rates of mental health problems have been identified in these regions [52].

Allowing for 10% non-participation for the pre-intervention testing, we expect the first data collection to include 540 children (270 in the control schools and 270 in the intervention schools). As the sample will represent a selected group of children from low SES areas rather than a random sample for all socioeconomic groups, there is evidence that attrition and movement of students will be greater in this sample. Hence, we conservatively estimate that we will have lost 30% of students at the 12 month follow-up in Year 1 leaving 190 children in each of the groups (N = 380). This is approximately 30 children per school, which is double that required to have an 80% chance of detecting an effect for the movement variables in a nested design with 12 schools (approximately 15 students per cluster or N = 180).

This study will have a broad inclusion policy and all Pre-Primary children and their parents in the selected schools will be invited to participate in the project. Children from non English speaking backgrounds and those with diagnosed and undiagnosed disabilities or developmental delays will be included in the testing wherever possible and only omitted from the project if data collection is impossible. Children's ages will range from 4 years in the initial testing in Pre-Primary to 7 years in the final post test in Year 1.

School principals and parents will be provided with a detailed written description of the project: its purpose, procedures, risks and benefits and given an opportunity to ask research staff questions or seek clarification prior to signing assent (children) and consent (school principals and parents) to participate. Schools, parents and children will be advised that they are free to withdraw from the project at any time. This study has ethical approval from the Human Research Ethics Committee of Curtin University of Technology (approval number HR02/2009).

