### Analysis

This is a multivariate nested cohort design [51]. Schools will be randomly allocated to either the intervention or control condition and students will then be followed as a cohort over time to assess the effects of the intervention on a range of dependent variables. The outcomes for individuals can not be assumed to be independent and will be analysed as a Nested Analyses of Covariance (with covariates of sex and IQ) to assess the efficacy of the intervention program (2 groups × 3 testing times). This will be determined by a significant group x time interaction:

• *Hypothesis 1: *The *Animal Fun *program will result in a significantly greater improvement in fine and gross motor scores (measured by MABC-2 and BOT-2) compared with controls when comparing the pre-intervention score with post- intervention score in Pre-Primary and at 1 year follow-up.

• *Hypothesis 2*: The *Animal Fun *program will result in a significantly greater improvement in social skills (measured by SSRS) and perceived competence (measured by PSPCSA) compared with controls when comparing the pre- intervention score with post- intervention scores and at 1 year follow-up.

• *Hypothesis 3*: The Animal Fun program will result in a significantly greater improvement in behavioural problems (measured by SDQ and SSRS) compared with controls when comparing the pre- intervention score with the post- intervention scores and at 1 year follow-up score.

• BMI and girth measurements: These variables will be exploratory.

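### If the three-occasion nested ANCOVA is fitted in its classical form, children lost between Term 4 and Year 1 also leave the end-of-Pre-Primary comparison; a mixed model on all available scores would keep them

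*Protocol article*

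**What the plan says.** All references are to the protocol article.

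- **Analysis.** Because children within schools are not independent, outcomes are to be "analysed as a Nested Analyses of Covariance (with covariates of sex and IQ"), with 2 groups and 3 testing times. Efficacy is judged by a group by time interaction. Hypotheses 1 to 3 each claim a benefit at the end of Pre-Primary and again at 1 year.
- **Participants.** After a 10% allowance for children who do not take part, the authors write: "we expect the first data collection to include 540 children (270 in the control schools and 270 in the intervention schools"). On later loss they say: "we conservatively estimate that we will have lost 30% of students at the 12 month follow-up in Year 1". By their count, 190 per arm (380 in total) would then remain. The reason given is that "there is evidence that attrition and movement of students will be greater in this sample". The 380 are compared with a stated need of 180, about 15 per school in 12 schools.
- **Procedure.** The second testing is in Term 4 of Pre-Primary and the third in Term 3 of Year 1. All measures are repeated except the intelligence test, so IQ is measured once, at the first testing.

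The article does not name an estimation method, a rule for incomplete records, or the loss expected by Term 4.

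**The concern.** A classical repeated-measures ANCOVA works on complete rows: three scores plus sex and IQ. A child with valid baseline and Term 4 scores who moves away before Year 1 has an incomplete row and is deleted. The end-of-Pre-Primary result would then lose children because of something that happened after it was measured. The move into Year 1 falls between the second and third testing, so some of the expected loss may well occur there.

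Two things are at stake. One is precision at a time point that every hypothesis uses. The other, more important, is the assumption about missing data. The complete-case contrast is valid only if remaining in the study does not distort the arm comparison among completers. A likelihood-based analysis of all available scores allows dropout to depend on scores already observed, including the Term 4 score.

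IQ raises a smaller, related issue. Participants has a broad inclusion policy covering children from non-English-speaking backgrounds and children with disabilities or delays. The covariate includes verbal subscales. Any child without a usable IQ score would be deleted by the ANCOVA, and also by a mixed model unless a rule is given.

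**Working it through.** **1. The plan's own figures.** At 50 per school ("Schools will have 50 or more students (two or more classes) enrolled in Pre-Primary classes"), 12 × 50 × 0.9 = 540, as stated. 540 × 0.7 = 378, or 189 per arm, against the stated 380 and 190; this agrees within rounding. 15 × 12 = 180 also agrees. The abstract has different totals ("520 children aged 4.5 to 6 years will be recruited and it is anticipated that 360 children will be retained to the 1 year follow-up"), but 1 − 360/520 = 30.8% is about the same loss, so this point is unaffected.

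**2. How many children are at issue.** The expected loss by Year 1 is 540 − 380 = 160 (162 using 378). Children already gone by Term 4 are missing from that comparison under any method. Only those tested in Term 4 and lost later would be dropped by the choice of analysis. The article gives no split, so 160 is a ceiling.

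**3. Precision.** The variance of a school mean is proportional to (1 + (m − 1) × ICC)/m, where m is children per school. Completers only: m = 378/12 = 31.5. Nobody lost by Term 4: m = 540/12 = 45. With 10% lost by Term 4: m = 486/12 = 40.5. The article gives no ICC, so a range is assumed.

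Example at ICC 0.05: (1 + 30.5 × 0.05)/31.5 = 0.0802 and (1 + 44 × 0.05)/45 = 0.0711; √(0.0802/0.0711) = 1.062.

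| Assumed ICC | SE increase, 378 vs 540 | SE increase, 378 vs 486 |
|---|---|---|
| 0 | 19.5% | 13.4% |
| 0.01 | 13.8% | 9.7% |
| 0.02 | 10.6% | 7.5% |
| 0.05 | 6.2% | 4.5% |
| 0.10 | 3.5% | 2.6% |
| 0.20 | 1.7% | 1.3% |

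The middle column is the upper bound.

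**4. Power.** The stated 80% at N = 180 cannot be reproduced, because no effect size, SD, ICC or alpha is given. Instead, take the effect that has 80% power at 15 per school, assuming two-sided alpha 0.05, 6 schools per arm and a noncentral t with 10 degrees of freedom. Power for that effect is:

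| Assumed ICC | 378 children | 540 children |
|---|---|---|
| 0 | 0.98 | 1.00 |
| 0.02 | 0.95 | 0.98 |
| 0.05 | 0.91 | 0.94 |
| 0.10 | 0.88 | 0.90 |
| 0.20 | 0.84 | 0.86 |

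Power stays above 80% throughout.

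**5. What bias could look like, by assumption only.** Suppose retention is 70% in both arms. Suppose also that in controls alone it rises with the Term 4 score, by 0.3, 0.5 or 0.7 in log-odds per SD. Let the correlation between baseline and Term 4 scores be 0.65. The mean Term 4 score of retained controls then shifts by 0.088, 0.143 or 0.191 SD. Their baseline shifts by 0.65 times that, so the change score shifts by 0.35 times it: 0.03, 0.05 or 0.07 SD. The arm contrast in change is biased by that amount. Keeping every Term 4 score removes it. None of these inputs comes from the article.

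**6. Is the classical reading plausible?** In the Background, the pilot is reported as a MANCOVA on 87 teacher forms with F(3, 81) = 10.363 and F(1, 83) = 21.507. The reported partial η² values follow: 3 × 10.363/(3 × 10.363 + 81) = 0.277 and 21.507/(21.507 + 83) = 0.206. The error degrees of freedom fit ordinary least squares on 87 complete records with two groups and, by inference, two covariates (87 − 2 − 2 = 83; 83 − 3 + 1 = 81). This shows the group's earlier practice. It does not show what the trial will do.

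**The case against.** The strongest reply is that the article never states a completers-only rule. A nested group by time ANCOVA can be fitted as a mixed model that keeps partial records, and a condensed article commonly leaves missing-data handling to an analysis plan. This stands, and it is why the point is conditional. It does not remove the point, because the method that is named has a classical form that deletes incomplete records, and nothing in the article rules that form out.

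Four further objections also stand, and they limit the point:

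- Comparing the 380 expected at Year 1 with the 180 needed is cautious sizing at the most depleted visit. It does not confine the Term 4 analysis to those 380.
- A reader might infer from the attrition sentence that completers are a selected group. The article says only that loss will be greater in this low-SES sample than in a sample of all socioeconomic groups. It does not say that leavers differ from stayers, or that loss differs by arm. Schools are paired on SES, location and size, and equal retention (190 and 190) is expected.
- The bias of 0.03 to 0.07 SD is a product of assumed one-sided dropout. With the same mechanism in both arms and no treatment effect, it is zero by symmetry.
- Nothing in the article says that children from non-English-speaking backgrounds will lack an IQ score. That is a possibility to provide for, not a predicted loss.

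**Conclusion.** The point holds in conditional form. If the nested ANCOVA is fitted as a classical repeated-measures model, children tested in Term 4 but lost before Year 1 leave the end-of-Pre-Primary comparison as well. Their number is unknown and at most about 160 of 540.

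The precision cost is modest: at most about 6% in SE at an ICC of 0.05 and 14% at 0.01. These rest on assumed ICCs and on nobody being lost by Term 4. Power remains above the planned 80%, because the expected sample is about double the stated need and between-school variation limits what extra children add.

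The main reason to act is the stronger missing-data assumption of a complete-case analysis. The documents do not support the stronger readings a reader might take from this: that the plan restricts itself to completers, that 30% will certainly be discarded, or that the result will be biased. This is a worthwhile, inexpensive improvement to the stated method and not a demonstrated error in the trial's result.

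**What to change.** In the Analysis section, replace the nested ANCOVA with a linear mixed model for each outcome that uses every available score. Include arm by visit effects, sex and IQ, a random school effect, correlation between visits within a child, and small-sample degrees of freedom (for example Kenward-Roger) suited to 12 schools. Read the end-of-Pre-Primary and 1-year effects as separate contrasts from this model. Keep children with no baseline IQ by simple baseline imputation. Report the complete-case ANCOVA as a sensitivity analysis, and state how many children have Term 4 but no Year 1 scores, by arm.

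The cost is a few sentences of analysis wording and slightly more model specification, with no new data or recruitment. The small downside is reliance on missing-at-random, which is still weaker than what the complete-case analysis needs. The change should be made before outcome data are examined.
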